### Blinding

Treatment will be allocated by numbering the research subjects and including the right-back area as number 1 and the left-back area as number 2. We will use computer-generated randomization method [9] to determine the back area and the type of sunscreen to be given [10]. Neither the research subjects nor the researchers will be aware of the type of sunscreen that will be applied. The allocation data for each subject will be placed in a sealed opaque envelope. At the time of data collection, the envelope will be opened, and the sunscreen will be applied by the research assistant. Both randomization and treatment allocation will be carried out by statisticians. The data will not be accessed until data collection for all subjects is completed. The irradiation test and the assessment of results will be carried out by researchers.

### Data Collection Methods

Before data collection begins, a preliminary study will be conducted to determine the value of broadband ultraviolet B (BB-UVB) MED on various skin types as well as to conduct inter-reviewer reliability tests. The data will be obtained from the literature and the tool guide and used as a source of information on the differences in the test doses upon irradiation. Therefore, a preliminary study will be conducted to equalize the dose of the irradiation test. Reliability testing will be performed to achieve same perception to assess erythema to ensure the quality of the data produced during the research. The test will be carried out by showing 11 skin photos to 3 assessors to determine the MED of each photo [11]. After that, the readings of the 3 assessors will be compared based on the intraclass correlation (ICC). An ICC value close to one, in this study set at 0.9, indicates that the reviewer has the same understanding of the MED reading so that, in the study, the MED reading can be carried out by the researcher.

We will use inclusion and exclusion criteria to select the research subjects. We will provide explanations about the purpose and research method before research subjects sign a consent form. There will be 2 sessions in the study: the first one for basic data collection and research sample selection and the second one for providing treatment and executing the randomization process.

After the consent form is signed, we will conduct history taking, physical examination, and documentation. History of systemic disease, skin disease, daily activities, malignancies, and family history will be recorded. We will assess the skin type and identify any skin lesion on physical examination.

This study will use metal halide UV enhanced lamp BB-UVB in the active spectrum of 290-320 nm (The Daavlin Lumera) for UVB radiation test. The device will be calibrated before every data collection.

### Data Management and Statistical Methods

All data obtained on the research status will be recorded for further coding. The collected data will be analyzed using SPSS (version 20.0; IBM Corp). The analysis will be carried out in 2 stages: descriptive and inferential analyses. In descriptive analysis, each variable is explained according to the type of data. The distribution of numerical data is assessed by looking at the normality value. The distribution of normal data is displayed with the mean and SD values. Categorical data are displayed in the form of frequency and percentage tables. In the inferential stage, the hypothesis will be tested using paired *t* test or Wilcoxon test to assess the differences in the decrease in SPF levels in each group of inorganic and organic sunscreens, and between the 2 groups. We used a 1-sided CI approach in the statistical analysis. The mean difference in SPF will be no different if the *P* value for the paired *t* test is >.05, and the upper limit of the CI does not exceed 4 SPF.

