**Methods:**

This study is a randomized, split-body, double-blind, noninferiority, and multicenter clinical trial in Cikini, Jakarta, Indonesia. An estimated 22 athletes in each group, who aged 18-40 years and practice in the morning or afternoon, will be randomized using a computer-generated randomization method. We calculated the sample size using the difference in the average decrease in sun protection factor (SPF) levels that is considered significant based on the clinical judgment set by the researchers, which was 5. Neither the research subjects nor the researchers are aware of the type of sunscreen that will be applied. The hypothesis will be tested using paired-sample t test or Wilcoxon to assess the difference of SPF levels in each group between organic and inorganic sunscreens with SPSS (version 20.0; IBM Corp).

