### Outcomes

This study will provide mean differences in SPF by 4 to establish noninferiority with a 95% lower confidence limit. The hypothesis will be tested using paired samples *t* test or Wilcoxon test to assess the difference of SPF levels in each group between organic and inorganic sunscreens. The difference in SPF level will be declared to be no different if the *P* value for the paired *t* test or Wilcoxon test is >.05, and the upper limit of the CI does not exceed 4 SPF level. The persistence of organic and inorganic sunscreens is assessed using the following parameters: (1) the MED is defined as the dose of UV radiation that induces just perceptible erythema on exposed skin 24 hours after irradiation. This MED result will be stated in mJ/cm^2^. (2) SPF is defined as the ratio of MED between protected and unprotected skin areas. The average SPF value from each type of sunscreen will be computed. The SPF value will be rounded up to one decimal in the index unit. (3) Persistence of SPF is defined as the lowest differences of SPF value before and after 1.5 hours swimming, stated in index unit.

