### Sample Size Estimates

The calculation of the sample size was carried out using the continuous variable noninferiority test formula and the comparison of the mean of the 2 groups in pairs. From the 2 formulas, the largest number of samples was taken for further use in research. Based on the previous clinical trial and risk of dropout, we estimated a minimum sample size of 22 participants in each group. We calculated the sample size using the difference in the average decrease in SPF levels that is considered significant, based on the clinical judgement set by the researchers (ie, 5). In total, 22 experimental subjects and 22 control subjects will be adequate to reject the null hypothesis that the population means of the experimental and control groups are equal with a probability (power) of 0.9. The type I error probability associated with this test of this null hypothesis is 0.05.

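### The margin of 4 SPF is set on the mean difference, but the plan also allows a Wilcoxon analysis and fixes no interval for it

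*Protocol article*

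**What the plan says.** **Scale of the margin.** Outcomes states: "This study will provide mean differences in SPF by 4 to establish noninferiority with a 95% lower confidence limit". The margin is therefore 4 SPF on a mean.

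**Test.** The Abstract (Methods) states: "The hypothesis will be tested using paired-sample t test or Wilcoxon to assess the difference of SPF levels". Outcomes and Data Management and Statistical Methods offer the same two tests. None of these places gives a rule for choosing.

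**Decision.** Outcomes requires P>.05 from either test, "and the upper limit of the CI does not exceed 4 SPF level". Data Management and Statistical Methods repeats the requirement that "the upper limit of the CI does not exceed 4 SPF", but ties the P value to the paired t test only. It adds: "We used a 1-sided CI approach in the statistical analysis".

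**Normality.** In the description of the descriptive stage, Data Management and Statistical Methods says: "The distribution of numerical data is assessed by looking at the normality value". No test or cut-off is named.

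**Error rate.** Sample Size Estimates states: "The type I error probability associated with this test of this null hypothesis is 0.05".

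**The concern.** A noninferiority claim needs the margin, the estimate and the confidence limit to refer to the same quantity. Here the margin refers to a mean. The signed-rank test gives no interval for a mean. Its companion (Hodges-Lehmann) interval is for the pseudo-median, which equals the mean only when the paired differences are symmetric.

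The two decision sentences also disagree. Outcomes lets a Wilcoxon P value feed the decision without saying which limit goes with it. Data Management and Statistical Methods has no decision rule for Wilcoxon at all.

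If the data pick the route, the quantity compared with 4 may change with the shape of the sample. Suppose a minority of athletes lose much more protection with the inorganic product. The pseudo-median then lies below the mean, and noninferiority is easier to declare.

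**Working it through.** **Inputs from the article:** 22 athletes, each receiving both products (22 paired differences); margin 4 on the mean; 1-sided limit; alpha 0.05; power 0.9; sample-size difference 5.

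**Assumptions, because the article gives no figure or rule:** the SD and skewness of the differences; Shapiro-Wilk P<.05 as the switch to Wilcoxon; a Hodges-Lehmann upper limit on that route. The difference d is the SPF decrease with inorganic minus the decrease with organic, so the upper limit is the one compared with 4, as in both decision sentences.

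**1. A plausible SD.** The sample size of 22 cannot be reproduced, since neither the SD nor the dropout rate is stated. Solving n = ((z₁ + z₂)·SD/δ)² for the SD gives SD = δ√22/(z₁ + z₂):

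- δ = 5, 2-sided 0.05: 5 × 4.690/(1.960 + 1.282) = 7.23
- δ = 5, 1-sided 0.05: 5 × 4.690/(1.645 + 1.282) = 8.01
- margin 4, 1-sided 0.05: 4 × 4.690/(1.645 + 1.282) = 6.41
- margin 4, 1-sided 0.025: 4 × 4.690/(1.960 + 1.282) = 5.79

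The 22 includes an unstated dropout allowance, so the SDs actually used would be somewhat lower. The range examined is 4 to 9.

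**2. Mechanism.** Take exponential-shaped differences with mean 4 and SD 7. In SD units the mean of an exponential is 1 and its pseudo-median is 1.678/2 = 0.839. The pseudo-median of d is 4 − 7 × (1 − 0.839) = 2.87. The Wilcoxon-based limit is then centred on 2.87 while the margin refers to 4.

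**3. False noninferiority, confidence-limit condition alone.** At least 5,000 simulated trials per setting, true mean difference exactly 4, nominal rate 0.05:

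| Shape of paired differences | Fixed t limit | Switching rule |
|---|---|---|
| Normal | 0.05 | 0.05 |
| Difference of two equally skewed decreases (symmetric) | 0.05 | 0.05 |
| Right skew 1.0 (gamma) | 0.08 | 0.10 |
| Right skew, lognormal with sigma 0.5 | 0.10 | 0.15 |
| Right skew 2.0 (exponential) | 0.11 | 0.20–0.21 |
| Left skew (reversed exponential) | 0.02 | 0.01 |

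Under right skew the ratio of switching to fixed t runs from about 1.4 (skew 1.0) through 0.15/0.10 = 1.5 to about 2 (exponential). These rates do not depend on the SD.

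**4. Full written rule: P>.05 as well as the limit.** Switching rule:

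| SD of differences | Lognormal | Exponential |
|---|---|---|
| 4 | about 0 | about 0 |
| 5 | under 0.01 | under 0.01 |
| 6.4 | 0.08–0.09 | 0.10–0.11 |
| 7 | 0.12 | 0.15–0.16 |
| 9 | 0.15 | 0.20–0.21 |

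The SD matters here because of the P>.05 condition. On the t route the limit condition is mean ≤ 4 − 1.721·s/√22, and the P condition is |mean| ≤ 2.080·s/√22. For positive means the two bounds meet at s = 4 × 4.690/(1.721 + 2.080) = 4.94. Below that observed SD the P condition is the tighter one and blocks most false claims.

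**5. Like for like, P>.05 kept in both rules, fixed t against switching:** lognormal 0.048 against 0.084 (SD 6.4) and 0.074 against 0.121 (SD 7.2); exponential 0.036 against 0.102 and 0.075 against 0.167.

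**The case against.** A reader might infer that the plan states a normality-driven switch and that any skewness then doubles the error rate. The article does not support either step.

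- The normality sentence belongs to the descriptive stage, and nothing says outright that it selects the test. This stands. Selection by normality is the natural reading of a choice between these two tests, but it remains an inference.
- The Hodges-Lehmann limit appears nowhere. A t interval beside a Wilcoxon P value is not excluded and fits a margin on the mean. On that reading the full rule gives about 0.06 at SD 6.4 and 0.075 to 0.08 at SD 7 under the two right-skewed shapes in step 4. This also stands. The text permits that reading but does not fix it.
- Inflation needs the paired difference itself to be right-skewed. The article gives no reason to expect this, and in a split-body design two equally skewed decreases give a symmetric difference. This limits the size of the effect.
- A fixed t limit used alone runs at 0.10 to 0.11, so against the full written rule it gains nothing at SD 6.4 and only a modest amount at SD 7. This is true in total error. But the restraint comes from requiring a nonsignificant difference, which fades as the SD grows and does not tie the limit to the mean.
- Normality tests and cut-offs are commonly left to an analysis plan. Agreed, and their absence is not the point. The point is that the stated decision rule admits a test with no interval for the quantity on which the margin is set.

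**Conclusion.** The defect holds without any simulation: the margin is on a mean, one permitted route has no interval for that mean, and the two decision sentences differ on whether Wilcoxon enters at all.

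Its size is conditional. It rests on the assumed switch, a Hodges-Lehmann limit compared with 4, clearly right-skewed differences and an SD of about 6.4 or more. Under those conditions the full rule gives a false noninferiority rate of roughly 0.08 to 0.21 instead of 0.05. At an SD of 5 or less, with symmetric or left-skewed differences, or with a t interval throughout, the rate is near or below 0.05, or at most modestly above it. A general statement that skewed data double the error would go too far: against the fixed t limit, only the exponential shape reaches a factor of about two on the limit condition alone. The point merits a correction, but it does not show that the trial's conclusion is wrong.

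**What to change.** In both Outcomes and Data Management and Statistical Methods, state that the noninferiority decision rests on the 1-sided 95% paired-t upper limit for the mean within-athlete difference in SPF decrease (inorganic minus organic), compared with 4, whatever the normality check shows. Report the Wilcoxon test with a Hodges-Lehmann interval as a labelled sensitivity analysis only.

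The cost is one sentence in each section and no new data. The article's Results section says the analysis was carried out in January-March 2021, so the report should also say which interval was used and give the t-based limit.

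There are two downsides. With 22 pairs the t limit itself runs at about 0.10 under strong right skew, so the fix removes only the part of the excess due to Wilcoxon. Resting the decision on the limit alone also drops the P>.05 condition, and with it that condition's incidental restraint at small SDs.

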## Methods

### Study Aims and Objectives

First, this study aims to assess whether inorganic sunscreen is as good as organic sunscreen in the field of the persistence of sunscreens after swimming for 1.5 hours. SPF of inorganic and organic sunscreens will be calculated before and after swimming training. The difference between those times will be measured and compared. SPF will be quantified using the minimal erythema dose (MED) test that will be conducted in 2 days. Irradiation will be carried out on the first day, and MED results will be collected 24 hours after irradiation.

Second, we assess the SPF value resulting from in vivo method conducted before swimming. The SPF of either organic or inorganic sunscreens will be compared in the manner of MED. This trial also aims to know the decreasing level of SPF after swimming for 1.5 hours and which type of sunscreen provides higher persistence.

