### Study Design and Setting

This is a randomized, split-body, double-blind, noninferiority, multicenter clinical trial. The recruiting center is Cikini swimming pool, located in Jakarta, Indonesia. Recruitment began in August 2020 and ended in December 2020.

Research subjects were selected from Cikini swimming center in Jakarta, Indonesia. Data collection will be carried out on the same person using the split-body method. Each research subject will receive 2 treatments in the form of inorganic and organic sunscreens. The sunscreen application will be executed on the back area on the right and left for each treatment simultaneously.

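### The success rule adds a non-significance condition (P > .05) to the confidence limit, so a significantly better inorganic sunscreen, or a precisely estimated small deficit inside the margin, fails

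*Protocol article*

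**What the plan says.** The Study Design and Setting section describes the trial as follows: "This is a randomized, split-body, double-blind, noninferiority, multicenter clinical trial". The first aim is to "assess whether inorganic sunscreen is as good as organic sunscreen in the field of the persistence of sunscreens", which asks about one direction only. A further aim is to learn "which type of sunscreen provides higher persistence".

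The decision rule appears twice. The Outcomes section begins it with "The difference in SPF level will be declared to be no different if the" and continues with two conditions joined by *and*: the P value for the paired t or "Wilcoxon test is >.05, and the upper limit of the CI does not exceed 4 SPF level". Data Management and Statistical Methods gives the same pair of conditions for the paired t test: "test is >.05, and the upper limit of the CI does not exceed 4 SPF". It adds: "We used a 1-sided CI approach in the statistical analysis". The sidedness of the P value is not given.

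The Outcomes section also opens with a sentence that mentions no P value: "mean differences in SPF by 4 to establish noninferiority with a 95% lower confidence limit".

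Sample Size Estimates gives 22 participants in each group, a difference of 5 SPF, power 0.9 and type I error 0.05. It defines that power as the chance of rejecting equal means.

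**The concern.** A noninferiority claim needs one thing: the confidence limit on the unfavourable side must stay within the margin. Here the test of zero difference must also be non-significant. That has three consequences.

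- A significant result in favour of inorganic gives P below .05, so the rule fails although the limit lies far inside the margin.
- A small deficit that is estimated precisely enough to differ from zero fails too, even when the whole interval lies below 4.
- Absence of significance is treated as support for sameness. A noisier trial meets that half of the rule more easily.

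The power statement then points the other way. The trial is sized to reject equality, and rejecting equality is the result that this rule counts as failure. What is at stake is the primary verdict.

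**Working it through.** **Inputs from the article.** 22 per group, read as 22 pairs because each athlete receives both products; margin 4; planning difference 5; alpha 0.05; power 0.9; one-sided CI. **Not given:** the SD of the paired difference, the dropout rate, the sidedness of P and the direction of the difference. I take D = decrease on inorganic minus decrease on organic, so a negative D favours inorganic.

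**Step 1: the stated sample size.** Without an SD, n = 22 at 0.9 power cannot be reproduced. It can only be solved backwards for the SD, using the noncentral t with 21 degrees of freedom and noncentrality difference × √22 / SD:

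| Difference | Test | SD giving power 0.9 |
|---|---|---|
| 4 | two-sided .05 | 5.52 |
| 4 | one-sided .05 | 6.20 |
| 5 | two-sided .05 | 6.90 |
| 5 | one-sided .05 | 7.75 |

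These values ignore the unspecified dropout allowance.

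**Step 2: where each condition bites.** With standard error SE = SD/√22, t(.95) = 1.721 and t(.975) = 2.080:

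- limit condition: mean D ≤ 4 − 1.721 × SE
- two-sided P > .05: |mean D| < 2.080 × SE

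At SD 6.90, SE = 6.90/4.690 = 1.471. The limit condition is met at any mean D up to 4 − 2.53 = 1.47. The P condition needs |mean D| below 3.06. So every observed advantage for inorganic larger than 3.06 fails, while on the deficit side the limit is already the stricter condition.

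At SD 3 (an illustration of high precision), SE = 0.640. The limit allows mean D up to 2.90, but the P condition cuts off at 1.33. Observed deficits between 1.33 and 2.90 lie within the margin and fail.

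The P condition becomes the stricter one on the deficit side when 2.080 × SE < 4 − 1.721 × SE. That is SE < 4/3.801 = 1.052, or an SD below about 4.9.

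**Step 3: chance of passing.** Simulation with 22 pairs, normal differences, one-sided 95% limit and two-sided P. Each cell shows limit alone / joint rule, in %:

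| SD | D = −5 | D = −3 | D = 0 | D = +2 |
|---|---|---|---|---|
| 5.52 | 100 / 2 | 100 / 32 | 95.0 / 91.8 | 50 / 46 |
| 6.20 | 100 / 5 | 100 / 42 | 90.2 / 87.4 | 43 / 42 |
| 6.90 | 100 / 10 | 99.8 / 50 | 83.8 / 81.2 | 37 / 37 |
| 7.75 | 100 / 18 | 99.3 / 58 | 75.7 / 73.2 | 32 / 32 |

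At D = 0 the loss cannot exceed 5 points, because P > .05 then holds in 95% of trials. At SD 3 and D = +2 the figures are 91.6% and 15.3%.

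**Step 4: other sidedness.** If P is one-sided towards inferiority, then at SD 6.90 the joint rule gives 99.8% at −3, 100% at −5 and 83.5% at 0, so the loss for a better product is gone. At SD 3 and D = +2 it still falls from about 92% to 8%.

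**Step 5: false claims.** At D = +4 and SD 6.90 the limit alone passes in 5.0% of trials and the joint rule in slightly fewer (about 4.8%). An added condition cannot raise this rate.

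**The case against.** **A criterion without a P value exists.** The opening sentence of Outcomes ties 4 SPF and a confidence limit to noninferiority, and the joint rule is attached to the words for no difference. This is a fair reading, but that sentence is not a complete rule. It names a lower limit, the rule names an upper one, and neither says which product is subtracted from which. The joint rule is the only one fully stated, and it appears twice. If it was meant as equivalence it would still be wrong, because it bounds one side only and relies on non-significance.

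**The large losses need a two-sided P and a better inorganic product.** Both parts stand. Two-sided is the usual form of a paired t test, but the article does not say so. The Introduction expects organic to last longer, and on that side at SD 6.90 the P condition costs almost nothing.

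**The error is conservative.** This stands: the harm is missed or wrongly negative verdicts, not false claims of noninferiority.

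**Two stronger readings should be resisted.** A reader might infer that the extra condition uses up part of the stated 0.9. It does not, because that figure is the power to reject equality and was never the power of this rule. A reader might also infer that the rule prevents the trial from saying which product persists better. It does not: Data Management and Statistical Methods plans a between-group test of the decrease, and its direction answers that question.

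A confidence limit to match the Wilcoxon test, and the handling of non-normal data, can be left to an analysis plan and are not part of this point.

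**Conclusion.** The rule is wrong as written and can return the wrong primary verdict. Under 22 pairs, a back-solved SD of about 5.5 to 7.75, a two-sided P and a one-sided 95% limit, a true inorganic advantage of 3 SPF passes in about 32% to 58% of trials instead of at least 99%. At no true difference the loss is modest, about 2.5 to 3 points. A precisely estimated small deficit fails whichever sidedness is used, but this matters mainly if the SD is well below the back-solved range.

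That a better product fails is not established for every reading of the article: it depends on P being two-sided. The exact sizes depend on an SD that the article does not give. What needs neither assumption is that non-significance has no place in a noninferiority criterion, and that the 0.9 describes the chance of a result that, with a two-sided P, this rule counts as failure in either direction.

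**What to change.** - Delete the P > .05 condition in Outcomes and in Data Management and Statistical Methods.
- Declare noninferiority if the one-sided 95% upper limit for the mean of (decrease on inorganic minus decrease on organic) is below 4.
- Write that direction into Outcomes and bring the sentence about a lower confidence limit into line with it.
- For the secondary question, read superiority from the same analysis.
- In Sample Size Estimates, either label the 0.9 as power to reject equality, or give the power of the noninferiority rule together with the SD it assumes.

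The cost is a few sentences and no new data. However, the Results section says that the analysis was conducted in January-March 2021. The change should therefore be disclosed as made after analysis, and the verdict reported under both the published rule and the corrected one.
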